## 2 Study Overview

### 2.1 Introduction

This document is the Statistical Analysis Plan (SAP) for “**A randomized, double-blind, placebo-controlled Phase III clinical trial to evaluate the efficacy and safety of SCTV01E (A COVID-19 Alpha/Beta/Delta/Omicron Variants S-Trimer Vaccine) in healthy adults aged  $\geq 18$  years**”, and mainly describes specific statistical analysis methods used to analyze and report baseline characteristics of participants and efficacy and safety evaluation data. The relevant statistical analysis results of this study may be used for the registration application of this product.

This SAP will be finalized and approved prior to database lock, and the corresponding statistical analysis programming will be refined as study data accumulate until database lock.

Sample statistical analysis tables for this SAP will be provided separately as attachments.

### 2.2 Analytical purpose

The purpose of this SAP is to describe specific statistical analysis methods used to analyze and report baseline characteristics of participants and efficacy and safety evaluation data. The corresponding statistical analysis results will be presented in the final clinical study report, and will also be used for registration application, article publication, and other clinical needs of this product.

Post-hoc exploratory analysis allows for further analysis of study data, but is not presented in this SAP due to unpredictability. Post-hoc exploratory analysis, if conducted subsequently, will be detailed in the final statistical analysis report or the final clinical study report.

Additional analysis for other purposes, such as article publication and requirements of regulatory authority or sponsor, is also not presented in this SAP due to unpredictability. The corresponding statistical analysis methods for additional analysis, if conducted subsequently, may not be detailed in the final clinical study report, but will be detailed in the document presenting the additional analysis results.

### 2.3 Changes in statistical analysis from the protocol

The statistical analysis planned in this SAP is consistent with those specified in the protocol.

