Participants in the SS set are the main analysis population for safety.

Participants in the I-PPS set are the main analysis population for immunogenicity. Particularly, participants with evidence of SARS-CoV-2 infection prior to the target date of the analysis (e.g. 28 days after the study vaccination) will be excluded from the immunogenicity analysis.

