#### **Statistical analysis methods:**

##### **Efficacy analysis**

Analysis of the primary endpoint will be performed based on PPE.

Primary endpoint: The vaccine efficacy will be estimated with 1-HR using a Cox proportional hazard regression model with separate baseline strata of age (18-59 years,  $\geq 60$  years) and the type of the last dose of COVID-19 vaccine previously received (inactive, non-inactive). Events that coincide in time will be processed based on the Efron method.

Subgroup analysis of the primary efficacy endpoint will be performed to assess the consistency of vaccine efficacy, such as different ages (18-59 years,  $\geq 60$  years), and the type of the last dose of COVID-19 vaccine previously received (inactive, non-inactive).

Details of the sensitivity analysis are described in section 11.4.4.

Similar statistical analysis model will be applied to VE assessment for both the primary endpoint and second endpoints.

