**Immunogenicity Analysis**

The Immunogenicity analysis will be based on I-PPS.

The GMT of neutralizing antibody for each group with corresponding 2-sided 95% CI will be estimated.

Comparisons between groups were based on age (18-59 years,  $\geq 60$  years) and the type of last dose of COVID-19 vaccines (inactive, non-inactive) as fixed effects ANOVA model

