**(7) Immunogenicity per-protocol evaluable (I-PPE)**

It includes the susceptible population in the PPS with negative PCR results at baseline (baseline IgG < 338 BAU/mL). The I-PPE is the primary analysis population for immunogenicity. Particularly, for participants with evidence of SARS-CoV-2 infection, post-infection immunogenicity data will be excluded from analysis, and pre-infection immunogenicity data may still be included.

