#### **7.6 Efficacy evaluation**

##### **7.6.1 Primary efficacy evaluation**

✧ **Protective efficacy of the study vaccine against symptomatic infection of SARS-CoV-2 after 7 days post vaccination ( $\geq 8$  days) versus placebo**

The Cox proportional hazards model is used to statistically analyze the protective efficacy of the study vaccine against symptomatic infection of SARS-CoV-2 after 7 days post-vaccination, with the person-years at risk as the dependent variable and with the age (18–59 years,  $\geq 60$  years), the vaccine type of the last previous dose (inactivated, non-inactivated), and the group as fixed effects. The protection rate of the vaccine and its 95% confidence interval are calculated according to the model. Events that coincide in time are handled based on the Efron method. If the model reaches convergence, the stratification factor of the vaccine type of the last previous dose will be removed from the model first; if the model still converges, the age stratification factor will be further removed.

Person-years at risk of the primary endpoints = (End/censored time of valid case surveillance period - Vaccination time - 7) / 365.25; where, the end/censored time of valid case surveillance period is calculated according to the following rules:

- For those who have symptoms and are diagnosed with COVID-19 before the data cut-off date, the end time is the start date of the first symptom (first onset date) of the target event or the date of the positive result for antigen or nucleic acid tests corresponding to the event, whichever comes earlier;
- For those with positive results of rapid antigen and/or laboratory RT-PCR tests post vaccination before the data cut-off date, but not diagnosed with the target event, the censored time is the earlier of the sampling dates corresponding to the positive results for antigen and RT-PCR tests;
- For those with negative results of rapid antigen and/or laboratory RT-PCR test post vaccination before the data cut-off date, but not diagnosed with the target event, the censored time is the last follow-up date of the case surveillance;
- For those vaccinated with other COVID-19 vaccines before the data cut-off date, the censored time is the date of first vaccination with other COVID-19 vaccines; those diagnosed with target events after vaccination with other COVID-19 vaccines are not included in the case count.

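### SAP 2.3 declares consistency with the protocol, but the primary Cox model and the main immunogenicity population and model differ between the two documents

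*Combined protocol and SAP*

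**What the plan says.** SAP 2.3 is a single sentence: "The statistical analysis planned in this SAP is consistent with those specified in the protocol". Three places in the two documents do not agree with it.

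- **Primary model.** The protocol synopsis (Efficacy analysis) estimates vaccine efficacy "using a Cox proportional hazard regression model with separate baseline strata of age" and type of last COVID-19 vaccine dose. SAP 7.6.1 also uses a Cox model, but lists age, "the vaccine type of the last previous dose (inactivated, non-inactivated), and the group as fixed effects".
- **Main immunogenicity set.** The synopsis (Statistical populations) says: "Participants in the I-PPS set are the main analysis population for immunogenicity". SAP section 6, item (7), says: "The I-PPE is the primary analysis population for immunogenicity". I-PPE is limited to PPS members who are PCR-negative at baseline with IgG below 338 BAU/mL. It is not among the sets defined in the synopsis. SAP 7.6.2.2.1 bases the main prime-immunization results on I-PPE and analyses I-PPS as well.
- **Immunogenicity model.** The synopsis (Immunogenicity Analysis) compares groups with age and last-dose type "as fixed effects ANOVA model"; no baseline titre is named. SAP 7.6.2.2.1 uses a covariance model with the log pre-vaccination titre as covariate.

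Protocol version 6.0 and SAP V1.0 carry the same date, 5 May 2023.

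**The concern.** SAP 2.3 is where a reader looks to learn whether the SAP has replaced anything in the protocol. Here it reports no change although a model and a main population have been replaced.

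For the primary endpoint, one hypothesis (VE above 30%, one-sided 0.025) has two specified models. SAP 7.6.2.1 reuses the primary method for the secondary efficacy endpoints, so the mismatch runs through the ten-step testing sequence in SAP 7.10. The protocol's stratified model does not appear even as a sensitivity analysis: the two in SAP 7.6.1 are an exact Poisson regression and a Cox model with group alone.

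For immunogenicity, the headline titre ratio would be estimated in different people depending on which document is followed. A ratio among PCR-negative people with low baseline antibody answers a different question from one in all protocol-compliant subgroup members.

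**Working it through.** **1. The two Cox models.** With two binary factors there are four strata.

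- Protocol synopsis: h(t) = h_s(t) × exp(β × group), with a separate baseline hazard h_s for each stratum s.
- SAP 7.6.1: h(t) = h_0(t) × exp(β × group + γ1 × age + γ2 × vaccine type), with one baseline hazard, and strata proportional to one another over time.

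These have different partial likelihoods, so this is more than a difference of wording.

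**2. The plan's own figure.** Inputs (protocol synopsis, Sample size estimation; SAP 4.3): 59 events, VE 70% (HR 0.3) against a null of 30% (HR 0.7), 1:1 allocation, one-sided 0.025.

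Schoenfeld power = Φ(|ln(0.3/0.7)| × √59 / 2 − 1.96) = Φ(0.847 × 3.841 − 1.96) = Φ(1.294) = 0.902.

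The stated 90% reproduces. The formula does not distinguish the two models, so it does not show which was intended.

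**3. How much the model choice matters.** Simulated trials used 2,623 participants and the Table S2 shares (29.7% aged 60 or over, 26.7% non-inactivated last dose), true HR 0.3 and Efron ties. The stratum effects are assumptions: log hazard ratio 0.5 for age and −0.3 for vaccine type. The baseline hazards were proportional in one scenario; in the other they were non-proportional by age (Weibull shapes 0.6 and 1.6). There were 150 trials per scenario.

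| | Proportional strata | Non-proportional strata |
|---|---|---|
| Mean events | 65.8 | 63.5 |
| VE, covariate / stratified | 70.2% / 70.2% | 71.9% / 71.9% |
| Mean absolute difference in lower limit | 0.19 points | 0.18 points |
| Largest difference | 1.3 points | 2.1 points |
| Verdict against 30% differs | 1.3% (2 of 150) | 0% (0 of 150) |

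A separate set of 1,500 simulated trials at 59 events gave 0.8% differing verdicts, a mean difference of 0.19 points and a 95th percentile of 0.65 points. Its stratum inputs are not available, so it serves only as agreement in order of magnitude.

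**4. What the immunogenicity restriction removes.** Inputs are from Tables S1 and S2.

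- IgG below 338 BAU/mL: 3,288 / 9,191 = 35.8%; at or above: 5,903 / 9,191 = 64.2%.
- PPE as a share of the FAS: 2,623 / 9,196 = 28.5%. PPE also drops infections within 7 days and makes other exclusions, so it is a reference point and not the size of I-PPE.

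If the subgroup has the FAS antibody distribution (an assumption), the IgG restriction alone leaves at most:

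- of the 200 persistence participants: 200 × 0.358 = about 72 (at the PPE share, 200 × 0.285 = 57);
- of a subgroup of 5% to 10% of the FAS (460 to 920): 460 × 0.358 = about 165, to 920 × 0.358 = about 329.

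The documents do not give the size of I-PPS, so the loss due to the switch from I-PPS to I-PPE cannot be isolated.

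**The case against.** The synopsis says that it gives the main methods and leaves details to the SAP. The SAP names a single primary model, is to be final before database lock (SAP 2.1), and assigns the analysis to an independent third party (SAP 7.11). The two Cox models almost always agree. Immunogenicity lies outside the testing sequence, and SAP 7.10 calls its P values nominal. I-PPS is still analysed for the prime immunization. The synopsis sentence on the ANOVA is terse, does not list group as a factor, and comes from a synopsis whose fuller protocol text is not in the file; a baseline covariate could be the kind of detail left to the SAP.

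Most of this stands, and it limits the consequence. It does not make SAP 2.3 true: a different baseline-hazard structure and a different named main population are substitutions, and the shared date rules out an older protocol version as the explanation. The ANOVA/ANCOVA difference is the weakest of the three, because it rests partly on silence.

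Four stronger readings are tempting but unsupported.

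- **The model could be picked after seeing results, or type I error is inflated.** The safeguards above argue against the first, and no inflation has been shown.
- **The immunogenicity mismatch undermines a confirmatory claim.** SAP 7.10 excludes that.
- **About 64% of the immunogenicity set is lost by moving to I-PPE.** That compares with the whole FAS, not with I-PPS.
- **The primary model collapses to an unadjusted one.** SAP 7.6.1 says: "If the model reaches convergence, the stratification factor of the vaccine type of the last previous dose will be removed from the model first". Read literally, this drops factors when the model succeeds. SAP 7.9 ties its own simplification to non-convergence, so a missing negation is the likelier explanation.

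**Conclusion.** The declaration in SAP 2.3 is wrong on the current text of both documents. That finding rests on comparison of the texts and needs no assumption.

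For the primary endpoint the numerical effect is small: about 0.2 points in the lower limit on average, and a changed verdict in about 0 to 1.3% of simulated trials. These figures depend on assumed stratum hazards and, with 150 trials per scenario, are imprecise. What remains is the need for one pre-specified model for the one-sided 0.025 test.

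For immunogenicity the choice is material to the headline estimate but not confirmatory. At most about 36% of the subgroup would meet the IgG restriction if it resembles the FAS. For persistence, SAP 7.6.2.2.2 mentions only I-PPE, so the protocol's main set has no stated analysis there.

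Severity: should-fix.

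**What to change.** 1. Name one primary model in both documents, for example the protocol's Cox model stratified by age and last-dose vaccine type, with the covariate-adjusted model as a sensitivity analysis. Name the two factors explicitly. A phrase such as stratified by the randomisation factors would bring in study site (SAP 4.2), which is in neither primary model.
2. Name one main immunogenicity population, report the other as supportive at every time point including persistence, and keep the ANCOVA with log baseline titre. Report the sizes of I-PPS and I-PPE by group.
3. Replace the SAP 2.3 sentence with a dated list of any departures that remain, with reasons. The file already contains results by group (Tables S4 to S6), so the date should show whether each clarification came before or after unblinding.
4. In the same edit, correct the convergence condition in SAP 7.6.1.

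The cost is wording in the protocol and SAP plus one additional model run per efficacy endpoint. No data collection changes.

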## 3. Study Objectives

### 3.1 Primary objective

To evaluate the protective efficacy of SCTV01E against symptomatic SARS-CoV-2 infection occurring 7 days after the study vaccine.

### 3.2 Secondary objectives

- To evaluate the protective efficacy of SCTV01E against all infections (including asymptomatic infection), asymptomatic infection, obvious symptomatic infection of SARS-CoV-2, moderate and above, severe and above COVID-19 and death due to COVID-19 occurring 7 days after the study vaccine, respectively;
- To evaluate the protective efficacy of SCTV01E against all infections (including asymptomatic infection), asymptomatic infection, symptomatic infection and obvious symptomatic infection of SARS-CoV-2 occurring 14 days after the study vaccination, respectively;
- To evaluate the protective efficacy of SCTV01E against infection of SARS-CoV-2 variants and subvariants occurring from 14 days after the study vaccination;
- To evaluate the immunogenicity of SCTV01E;
- To evaluate the safety of SCTV01E.

## 4. Study Design

### 4.1 Overall design

This study is a randomized, double-blind, and placebo-controlled Phase III clinical trial to evaluate the protective efficacy and safety of SCTV01E against COVID-19 in participants who were previously vaccinated with primary series of COVID-19 vaccines and /or received booster vaccination. This study includes a screening period, a period for randomization and vaccination, and a follow-up period (including follow-up for protective efficacy, immunogenicity, and safety). About 10000 participants will be enrolled in the study, with 5%–10% of participants in the immunogenicity subgroup. A screening visit will be conducted within 7 days after all participants sign the ICF. The participants who meet the inclusion and exclusion criteria will be randomized to the SCTV01E group or the control group at a ratio of 1:1. Participants in the SCTV01E group will receive one dose of SCTV01E on Day 0; participants in the control group will receive one dose of normal saline on Day 0.

**Protective efficacy evaluation:** Follow-up for protective efficacy will begin after vaccination. Study staff will ask participants for signs/symptoms related to COVID-19 by phone call, short message (SMS), email, or other means of communication. The follow-up for protective efficacy may be adjusted according to the progress of the trial. Meanwhile, participants can spontaneously report any COVID-19-related symptoms at any time during the study. Two nasal/nasopharyngeal/oropharyngeal swabs will be collected from the participant if any of the relevant COVID-19 clinical symptoms is/are met. One will be used for antigen rapid test and/or

SARS-CoV-2 reverse-transcriptase–polymerase-chain-reaction (RT-PCR) test; the other will be used for virus sequencing to determine which SARS-CoV-2 variant is infected if the participant is diagnosed with COVID-19 with any symptoms that meet the primary study endpoints. In addition, rapid antigen tests for SARS-CoV-2 nasal/nasopharyngeal/oropharyngeal swabs will be performed on Days 7 and 14. In order to guarantee that more accurate judgments are made for the collected COVID-19 cases, an Endpoint Assessment or Adjudication Committee (EAC) will be set up in this Phase III clinical trial to uniformly conduct independent evaluation and judgment on primary indicators.

**Immunogenicity evaluation:** Blood samples will be collected on Day 0 (pre-vaccination), Day 14 and Day 28 from participants in the immunogenicity subgroup (approximately 5%–10% of randomized participants), of which 200 participants need to undergo additional scheduled sampling on Day 7, Day 90 and other longer periods (detailed in the visit flow chart of the protocol) for the detection of SARS-CoV-2 (including mutant strains and mutant subtype) neutralizing antibody.

**Safety evaluation:** All participants will be observed at the study site for at least 30 minutes after the study intervention. Information is collected through a combination of active surveillance and spontaneous reporting. Solicited adverse events (AEs) within 7 days after vaccination and unsolicited AEs within 28 days after vaccination will be collected via vaccination record cards (VRCs). Serious adverse events (SAEs) and adverse events of special interest (AESIs) will be collected through active surveillance until the participant completes (or withdraws early from) the study.

This study will be conducted by Guizhou Center for Disease Control and Prevention, Sichuan Center for Disease Control and Prevention, and Hunan Provincial Center for Disease Control and Prevention.

## 4.2 Randomization

This clinical trial is a randomized and double-blind Phase III clinical trial. Participants will be randomized to the study vaccine group or the placebo group at a ratio of 1:1. To maintain relative balance between groups, participants will be stratified and randomized by age (18–59 years,  $\geq 60$  years), vaccine type of the last previous dose (inactivated, non-inactivated), and region (study site). Blind codes for participant randomization and blind codes for drug numbers will be generated and maintained by a third party.

Participants eligible for screening will be randomized by the Interactive Web Response System (IWRS) and vaccinated according to random numbers. For participants who withdraw from the study for any reason after randomization, regardless of whether they are administrated with the study

vaccine or not, their random numbers will be retained, and they shall not participate in the study again.

### 4.3 Sample size

After the adjustment of Beijing epidemic prevention and control policy, the protective efficacy of SCTV01E is between 70% and 77% in the real-world study. Therefore, assuming a protective efficacy (VE) of 70% (Hazard Ratio = 0.3) for the PPE population (as defined in the Analysis Set section) 7 days post-vaccination, in the condition of 59 cases, there is approximately 90% power to reject the null hypothesis  $H_0$  at a one-sided Type I error level of 0.025. The following assumption will be considered for sample size estimation and approximately 10000 participants (adjusted for actual infection rates) will be included. The final number of participants enrolled depends on the actual infection rate and the cumulative number of COVID-19 events. Of these participants, 5%–10% will be included in the immunogenicity subgroup.

- In the control group, the symptomatic infection of SARS-CoV-2 within 1 month is about 1.5%.
- The dropout rate during the study is about 10%.
- Approximately 15% of participants could not be included in the assessment of the number of events after 7 days because they are PCR positive at baseline or have an infection within 0–7 days after vaccination.

## 5. Evaluation Endpoints

### 5.1 Efficacy endpoints

#### 5.1.1 Primary efficacy endpoint

- ✧ Cases of the first occurrence of symptomatic infection of SARS-CoV-2 of any severity starting 7 days ( $\geq 8$  days) post-vaccination.

#### 5.1.2 Secondary efficacy endpoints

##### 5.1.2.1 Protective efficacy endpoints

- (1) Cases of first occurrence of obvious symptomatic infection of SARS-CoV-2 of any severity starting 7 days post vaccination;
- (2) Cases of first occurrence of all infections of SARS-CoV-2 (including asymptomatic infection) starting 7 days post-vaccination;
- (3) Cases of asymptomatic infection of SARS-CoV-2 infection starting 7 days post-vaccination;
- (4) Cases of first occurrence of moderate and above COVID-19 events starting 7 days

**post-vaccination;**

**(5) Cases of first occurrence of severe and above COVID-19 events starting 7 days post-vaccination;**

**(6) Cases of death due to SARS-CoV-2 infection starting 7 days post-vaccination;**

**(7) Cases of first occurrence of symptomatic infection of SARS-CoV-2 starting 14 days post vaccination ( $\geq 15$  days);**

**(8) Cases of first occurrence of obvious symptomatic infection of SARS-CoV-2 starting 14 days post-vaccination ( $\geq 15$  days);**

**(9) Cases of first occurrence of all infections of SARS-CoV-2 (including asymptomatic infection) starting 14 days post-vaccination ( $\geq 15$  days);**

**(10) Cases of first occurrence of asymptomatic infection of SARS-CoV-2 starting 14 days post-vaccination ( $\geq 15$  days);**

**(11) Cases of first occurrence of symptomatic infection of SARS-CoV-2 caused by SARS-CoV-2 variants and subvariants starting 14 days post-vaccination;**

**(12) Cases of first occurrence of obvious symptomatic infection of SARS-CoV-2 caused by SARS-CoV-2 variants and subvariants starting 14 days post-vaccination;**

**(13) Cases of first occurrence of moderate and above COVID-19 infection caused by SARS-CoV-2 variants and subvariants starting 14 days post-vaccination;**

**(14) Cases of first occurrence of severe and above COVID-19 infection caused by SARS-CoV-2 variants and subvariants starting 14 days post-vaccination;**

